##### Body fat percentage

will be measured by an Endo Body Fat Composition Analyser E-DBS908 (without shoes and socks) [46].

##### Waist circumference

will be measured by a non-stretch tape, standing up at the level midway between the lowest rib margin and the iliac crest and recorded to the nearest 0.1 cm [47].

##### Hip circumference

will be measured at the widest circumference at the level of the symphysis pubis and gluteus maximus [32].

##### Waist hip ratio

will be calculated as waist circumference divided by hip circumference [48].

##### Systolic and diastolic BP

will be taken from the left arm after consecutive measurements of the participants seated down and rested with an appropriate-sized cuff placed at the heart level using an Omron electronic BP monitor [49, 50].

##### Self-reported health-related quality of life (QOL)

using the Short Form (SF)-8 questionnaire will assess the health-related QOL and provide a brief overview of the physical, psychological and social domains of health to further support the study [51, 52].

##### Demographic data

including age, ethnicity, education, marital status, existing medical conditions, type of medications use and type of housing dwelling will be collected.

### Process evaluation

This will be undertaken throughout the intervention programme to determine reach (attendance); fidelity (quality of programme, programme delivery and resources), together with recruitment, dose delivered and received [53]. Criteria for assessing programme quality will take into account: (1) utility: information needs of participants are satisfied, e.g. usefulness of resources; (2) feasibility: cost-effectiveness, e.g. efficiency of evaluation process to justify use of available resources; (3) propriety: ethical standards are met, e.g. aggregated evaluation findings are made accessible to participants; and (4) accuracy: valid and reliable information, e.g. clear and accurate report documentation [54]. Structured feedback forms and focus group interviews will be undertaken with the participants to determine the effectiveness of programme and programme ambassadors; explore barriers, motivators; and satisfaction levels [55]. Collection of these data will provide information on the effectiveness of strategies, applicability of resources, and other factors that impact upon the delivery of the intervention [56]. These pertinent details will provide insight into programme implementation and factors that influence participation.

Exit interviews will be undertaken with programme completers (*n* = 12) and non-completers (*n* = 12). This sample size is considered adequate for non-probabilistic purposeful sampling [57]. Informed verbal consent will be obtained prior to conducting the interviews. The interviews will explore perception of the resources, the intervention and the programme ambassadors. Reasons for programme withdrawal will be obtained from non-completers. It is estimated that the face-to-face exit interviews will be of 20-min duration.

### Theoretical framework

Theoretical perspective underpinning this study is the SCT, which identifies the interaction of the individual with the social and physical environment, and how this interaction influences health behaviours in older adults [58-60]. It specifies a set of psychosocial constructs that include self-efficacy; outcome expectations (cognitive influences); observational learning and social support (environmental influences); as well as goal-setting and reinforcement (behavioural influences) which are described in Table 3 [61, 62]. In addition, Motivational Interviewing (MI) techniques will be used during the intervention delivered by the programme ambassadors. This is a person-centred, collaborative communication style, to raise commitment and reinforce behaviour change [63]. Studies on applied MI strategies have demonstrated its practicality in positively tackling unhealthy dietary and low PA levels [64, 65]. The use of these techniques in this study will support autonomy and heighten intrinsic motivation towards healthier lifestyles.

**Table 3 Tab3:** Application of Social Cognitive Theory (SCT) to inform strategies and methods

**SCT**	**Strategies**	**Methods**
Environment	Build physical and nutrition supports within the RCs	Conduct face-to-face meetings, follow-up calls and provide educational resources
Outcome expectations / Expectancies	Educate on the benefits of nutritious diet and regular PA / achievement of better health screening results and MI	Introduce concept of goal setting and resources at initial meeting; undertake face-to-face sessions, follow-up calls and feedback sessions
Self-efficacy	Goal setting, monitor progress and mastery of health practices and MI	Regular coaching and feedback on participants' PA and nutrition goals towards improving health outcomes (incremental and achievable). Programme ambassadors encourage the adoption of health-enhancing behaviour and practice of new skills and provide feedback
Observational learning	Observe programme ambassadors’ dietary and PA behaviours	Demonstrate PA and showcase cooking advice practices. Programme ambassadors act as positive role models
Positive reinforcement	Education and skill building sessions and MI	Regular encouragement, ongoing monitoring of personal PA goals through follow-up support and feedback

*MI* motivational interviewing, *PA* physical activity, *RC* recreational centre, *SCT* social cognitive theory

### Intervention

This 6-month community-based Singapore Physical Activity and Nutrition Study (SPANS) intervention programme will be based on the Singaporean PA and nutrition guidelines [66-68]. Programme ambassadors will undergo comprehensive training in MI and intervention programme and will undertake all the intervention activities and distribute the resources bi-weekly (see Table 4).

**Table 4: Tab4:** Singapore Physical Activity and Nutrition Study (SPANS) intervention

**Session (timing)**	**Session details**	**Participant’s resources / interactive activities**
**PA sessions** **(1 hr- twice a month)** **[Week 2 -24]**	1. Introduction to SPANS programme 2. **Focus PA:** aerobic • Benefits/barriers/motivators • Guidelines 3. Establish short and long term PA goals	1. **Resources** • ‘Active for Life’ booklet 2. **Interactive activities** • PA warm up • Muscle strengthening and low intensity aerobic workout • Cool down and stretches
**Nutrition session 1 – Eat Well, Live Well** **[Week 1]**	1. **Focus on nutrition** • Benefits/barriers/motivators • Healthy plate model and guidelines 2. Establish short and long term nutrition goals	1. **Resources:** • ‘Nutrition Guide for Healthy Aging’ booklet • Health calendar with monthly recipes and health tips 2. **Interactive activities:** • What’s On Your Plate? • Read your food label
**Nutrition session 2 – Smart Shopping and Dining Alert [Week 12]**	1. **Focus on nutrition** • Healthy shopping and cooking tips • Healthier Choice Symbols	1. **Resources** • ‘Recipes for Health Aging’ booklet • ‘Lowering BP’ booklet 2. **Interactive activities** • Ranking game on food calorie • Guess the herbs and spices in cooking
**Nutrition session 3 – Take Charge Of Your Health** **[Week 24]**	1. **Focus on nutrition and PA** • Manage cholesterol and BG levels 2. Identify social support and overcome relapse	1. **Resources** • ‘Keeping Cholesterol in Check’ booklet • ‘Tips to Better Health: Keeping My Blood Sugar Levels Healthy’ booklet 2. **Interactive activities** • Mix and match cholesterol in foods • Brainstorm on improving BG levels
**PA and nutrition counselling** **(45 mins – once every 2 months)** **[Week 4, 12, 20]**	1. **Focus on behavioural change** 2. Record dietary and PA record 3. Set, review short and long term goals 4. Provide guidance and support on healthy lifestyle	1. **Resources** • Fridge magnet with reminders on ‘Eat More Fruits and Vegetables’ • Tote Bag on ‘Healthy Living’ • Sports towel with ‘Warm Up Before PA’ slogan 2. **Interactive activity** • Goal setting and reflection
**Follow-Up Calls / PA and nutrition text phone messages** **(once per month)** **[Week 4 -24]**	1. A monthly PA and nutrition ‘tip of the day’ will be sent via a “WhatsApp” chat platform.	**Interactive activity** • Participants send other health-related messages to simulate discussion.

#### Group PA, nutrition talks, dietary counselling sessions and telephone contact

Bi-weekly, low-intensity PA, strength and balanced exercises sessions will be conducted. There will be bimonthly nutrition talks, bimonthly dietary counselling and monthly follow-up calls incorporating MI. Programme ambassadors will follow-up with participants’ enquires and provide feedback to support the adoption of healthy practices and monitor the progress of their participants’ goals. Participants will be encouraged to do moderate intensity PA for at least 150 min per week and reminded to monitor their daily progress and goals by recording the frequency and duration of PA in a health calendar provided at the commencement of the programme. Goal setting and feedback will be emphasized at all contact points during the intervention.

#### Educational resources

The programme ambassadors will introduce the 6-month intervention; distribute the resources throughout the intervention period; and ask participants to use the booklets as a guide to healthy ageing.

##### *Booklets*

‘*Active for Life*’: benefits of PA; guidelines for frequency, intensity, time and type of PA; and safety issues‘*Recipes for Healthy Ageing*’*– Nutrition Guide and Recipes*: my healthy plate model; dietary guidelines for older adults; tasty recipes; and healthy eating tips‘*Lowering BP*’ booklet: healthy BP range; problems of high BP levels; dietary sources of sodium; and ways to control and manage BP levels‘*Keeping Cholesterol in Check*’: dietary sources of cholesterol; ways to reduce dietary cholesterol; and recipe modification for better heart health‘*Tips to Better Health – Keeping my Blood Sugar Levels Healthy*’: pre-diabetes and diabetes; issues of high BG levels; and how do I control my BG levels?

#### Calendar

Participants will receive easy, healthy recipes found to enhance the adoption of healthy dietary behaviours among women of lower health literacy levels [69] in a *‘health calendar’* that contains health tips acting as reminders to stay active and eat healthily.

(These resources are available from the first author upon request).

#### Health text messaging

A nutrition and PA ‘tip of the month’ will be sent to all participants as text messages via "WhatsApp" on a monthly basis to motivate them to practice healthy lifestyle habits.

### Statistical analysis

After data collection, outcome variables of interest, such as blood profiles, self-reported PA and dietary behaviours, and anthropometric measures will be examined and compared between subgroups of interest via the Statistical Package for the Social Science version 24 [70]. Descriptive and summary statistics will be used to quantify participants’ characteristics and outcome variables. Non-parametric statistics will be applied whenever non-normality of the outcomes is detected. Multi-variable mixed regression analyses will be used to confirm the effects of the proposed intervention, taking into account the repeated measures (at two time points) and the clustering of the observations. All variables will be entered using the stepwise regression. The regression model will also account for effects of potential confounders (age, ethnicity, education, marital status, consumption of medication and housing type).

All qualitative data from process evaluation will be transcribed, with at least 10% of all transcribed data randomly selected and reviewed for each transcription. Transcribed data will be coded to create common themes or categories. Data will be collated, presented thematically and supported by direct quotes from participants. Data management of full transcripts and other texts will be facilitated by the NVivo software package [71] to conduct a framework analysis [72, 73]. Participants will not be identified in any transcription.

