**Methods:**

The development and implementation of the PA and nutrition intervention strategies will be guided by SCT and Motivational interviewing (MI) and implemented by trained programme ambassadors at the RCs. Sixty RCs located in Singapore will be selected from five major geographical districts and randomly allocated to the intervention (*n* = 30) or control (*n* = 30) cluster. A sample of 600 (intervention *n* = 300; control *n* = 300) women aged 50 years and above will then be recruited from these 60 centres and only the intervention group will be enrolled into the PA and nutrition intervention. It is hypothesised that by the end of the intervention, the intervention group participants compared to the control group will show significantly greater improvements in the following outcome variables: PA and dietary behaviours, health-related quality of life, objective measures of PA, anthropometric, lipid and glucose profiles. Data will be collected at baseline and 6 months and analysed using mixed regression models.

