## Methods

### Study design

A 6-month, community-based PA and nutrition cluster RCT suited to the Singaporean context will be implemented and evaluated over two time points (baseline and 6 months); see Table 1. A proposed schedule for enrolment, intervention and assessment is shown in the Standard Protocol Items: Recommendations for Interventional Trials (SPIRIT) Figure (Fig. 1) and recommended items to address for intervention trials are reflected in the Additional file 1: SPIRIT Checklist [21]. A flow chart of the research procedure is displayed in Fig. 2.

**Table 1 Tab1:** Proposed pre-post data collection and intervention

**Study group**	**(Baseline) 0 month**	**Intervention**	**(Post intervention) 6 months**
Controls (*n* = 300)	O1		O2
Interventions (*n* = 300)	O1	X	O2

*O* observation, *X* intervention

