#### Recruitment of participants

A sample of 600 (interventions *n* = 300; controls *n* = 300) women will then be recruited from these 60 RCs. Participants are required to be: (1) female, aged 50 years and above, (2) undertaking less than 150 min of moderate intensity leisure PA per week (self-reported), (3) not have any medical condition that prohibits involvement in a PA programme, and (4) not currently enrolled in other nutrition and PA research studies.

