#### Procedure

Programme recruitment flyers will be placed on the RC’s bulletin boards and promoted by the RC managers. Those residents indicating to the RC managers that they are interested in the programme and agreeing to provide their contact details will have their telephone number provided to the research team. These participants will then be telephoned to explain the purpose of the study and to determine their eligibility based on the selection criteria. After the initial telephone screening, eligible participants will be invited to take part, informed of their rights and confidentiality issues, and that they are free to withdraw at any stage.

At the initial meeting, baseline data will be collected and recorded using the health surveys available in the English and Chinese language reflected in the Additional files 3 and 4 [25-27]. Trained researchers (final-year tertiary students) will collect self-reported data on dietary habits and PA levels used to assess current dietary and PA levels and undertake anthropometric measures. These programme ambassadors are final-year nutrition, sports and wellness undergraduate students who will conduct their activities under close supervision of qualified nutritionists and certified fitness instructors. The principal investigator (PI) will fit and explain the management of the accelerometers. Fasting blood samples will be collected by a phlebotomist. Any participants exhibiting hypercholesterolaemia (total cholesterol (TC) ≥ 6.2 mmol/L) [28] or hyperglycaemia (BG > 7 mmol/L) levels [29] will be excluded from the study and referred to their medical practitioner for follow-up. Participants on medication will not be excluded and both the pre and post survey will document all those who are on medication including the type of medication and subgroup analysis will be undertaken.

Both the intervention and control participants who undergo pre and post data collection will be given an incentive of free health products (health calendar, sports towel, writing pad and pen with health messages) and supermarket vouchers in appreciation of their involvement in the study. However, the control group will be blinded to the nature of the intervention and instead only receive a falls prevention booklet.

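### The confirmatory mixed model uses baseline only as a second repeated outcome; fitted in the usual way, it tests continuous outcomes on change and gives up power that baseline adjustment would recover

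*Protocol article*

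**What the plan says.** The abstract gives two measurement waves and one family of models: "Data will be collected at baseline and 6 months and analysed using mixed regression models". The Statistical analysis section says that multi-variable mixed regression will confirm the intervention effect, "taking into account the repeated measures (at two time points) and the clustering of the observations". Both waves therefore sit on the outcome side. The same section names the adjustment set as "potential confounders (age, ethnicity, education, marital status, consumption of medication and housing type", and says of variable entry: "All variables will be entered using the stepwise regression".

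The baseline value of the outcome is not in the adjustment set. The section does not give the arm and time terms or the tested contrast, and it does not say whether baseline means may differ between arms.

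**The concern.** Every participant is to have a baseline value of the self-reported and blood outcomes, and that value is usually a strong predictor of the 6-month value. How the model uses it determines the precision of the between-arm comparison.

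In a two-wave mixed model with free arm means at both times, the treatment effect is the arm-by-time term. With complete data on a continuous outcome, that term is the difference between arms in mean change. It fixes the slope on baseline at 1 instead of estimating it.

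Two things follow. The test has more variance than the collected data require. A chance baseline difference between arms also carries through, in part, into the estimate. Stepwise entry adds a practical risk: a baseline term added later could be selected for one outcome and dropped for another unless it is forced into the model.

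**Working it through.** **No figure in the plan to reproduce.** The article states no power, correlation or intracluster correlation (ICC) for any continuous outcome. Its one sample-size figure, 240 per group, is for a binary activity prevalence of 28% against 38%, without covariate adjustment. The attrition step reproduces: 480/0.8 = 600. The 240 does not. Two-sided 5% and 80% power need (1.96 × √(2×0.33×0.67) + 0.8416 × √(0.28×0.72 + 0.38×0.62))² / 0.10² ≈ 346 per group before clustering. That is a separate matter and does not enter this point. I take only the cluster size from it: 240/30 = 8 analysed women per RC.

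**Assumed inputs.** Individual correlation rho 0.3 to 0.8; ICC 0, 0.02 or 0.05; correlation of the RC effects between waves (CAC) 0.8 or 1; equal variance at the two waves; a starting power of 80% on the change scale.

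**Step 1: the identity.** In 2,000 simulated two-wave data sets (240 per arm, no clustering), the unconstrained arm-by-time estimate equalled the difference in mean change to within 1e-14. Empirical standard errors were:

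| Analysis | rho 0.5 | rho 0.7 |
|---|---|---|
| Arm-by-time, free baseline means | 0.0903 | 0.0699 |
| Baseline as covariate | 0.0778 | 0.0647 |
| Two-wave model, common baseline mean | 0.0777 | 0.0646 |

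**Step 2: variance ratio without clustering.** In units of SD², the variance is proportional to 2(1−rho) for change and 1−rho² for baseline adjustment. The ratio, adjusted to change, is (1+rho)/2. Adjusted power is Φ[(1.96 + 0.8416)/√ratio − 1.96].

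| rho | 2(1−rho) | 1−rho² | ratio | power, from 80% |
|---|---|---|---|---|
| 0.3 | 1.40 | 0.91 | 0.65 | 93.5% |
| 0.5 | 1.00 | 0.75 | 0.75 | 89.9% |
| 0.7 | 0.60 | 0.51 | 0.85 | 86.0% |
| 0.8 | 0.40 | 0.36 | 0.90 | 84.0% |

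Read the other way, if the adjusted test had 80% power, the change test would have 61.7%, 67.9%, 73.3% and 75.7%.

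**Step 3: with clustering.** Replace rho by the RC-mean correlation R = [ICC×CAC + (1−ICC)×rho/8] / [ICC + (1−ICC)/8]. At rho 0.5:

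- ICC 0.02: R = (0.016 + 0.06125)/0.1425 = 0.54 (CAC 0.8) to (0.02 + 0.06125)/0.1425 = 0.57 (CAC 1). The ratio is 0.771 to 0.785, and power 89.1% to 88.5%.
- ICC 0.05: R = 0.099375/0.16875 = 0.59 to 0.109375/0.16875 = 0.65. The ratio is 0.794 to 0.824, and power 88.2% to 87.0%.

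A simulation with 30 RCs per arm and CAC 1 (4,000 trials) gave ratios of 0.765, 0.787 and 0.843 for ICC 0, 0.02 and 0.05. These are close to the formula and slightly less favourable.

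**Step 4: chance imbalance.** If the intervention arm starts higher by d through chance, the change estimate shifts by about −(1−R)d. At rho 0.5 this is 0.50d without clustering, 0.43d to 0.46d at ICC 0.02, and 0.35d to 0.41d at ICC 0.05.

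**The case against.** The strongest objection is that the article never states a change-score test. A reader might infer one from the wording, but a repeated-measures model with a common baseline mean fits the same words, and Step 1 shows that it loses nothing. Model terms are often left to a statistical analysis plan. This stands to the extent that the loss is conditional on the usual fit. It does not remove the point: the article fixes both waves as outcomes, gives an adjustment set without baseline, and writes no baseline constraint.

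Four other stronger readings are tempting and are not supported:

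- **That every primary outcome is affected.** The powered outcome is binary in a logistic mixed model, where the identity is not exact. Eligibility requires "undertaking less than 150 min of moderate intensity leisure PA per week (self-reported", so baseline activity status is nearly constant and adjusting for it would add little. The Accelerometers section describes fitting the devices to intervention participants only, so no between-arm change test is available there. The section also sends non-normal outcomes to non-parametric methods.
- **That the estimate is biased by regression to the mean.** The shift in Step 4 is conditional on the observed imbalance. Over repeated randomisation the change estimate is not biased.
- **That all baseline imbalance behaves this way.** Under Recruitment of RCs, five districts were allocated, three against two. Stable district differences do not regress to the mean. A change contrast removes them, while a baseline covariate can leave part of them. This is a real argument for keeping the change contrast in the plan.
- **That the eligibility cut-offs invalidate baseline as a repeated outcome.** The blood criterion reads "Any participants exhibiting hypercholesterolaemia (total cholesterol (TC) ≥ 6.2 mmol/L) [28] or hyperglycaemia (BG > 7 mmol/L) levels [29] will be excluded from the study". With complete data the unconstrained estimate is the difference in mean change whatever the two variances are, and no equal-variance structure is stated. If the cut-offs shrink the baseline variance, the gain for cholesterol, glucose and activity may be smaller than the equal-variance figures.

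**Conclusion.** The point holds as an efficiency concern for continuous between-arm outcomes, conditional on the usual unconstrained arm-by-time fit. Baseline adjustment would then cut the variance to (1+R)/2 of its value. From an assumed 80%, power rises by about 4 to 14 points for rho 0.8 to 0.3 without clustering, and by about 7 to 9 points at rho 0.5 with an ICC of 0.02 to 0.05. Rho, ICC, CAC, equal variances and the starting power are all assumptions. The stated 480 and 600 are not affected, since they rest on a binary outcome without covariates. The change is worth making because it uses data already planned and costs almost nothing. It does not show that the planned analysis is invalid.

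**What to change.** In the Statistical analysis section, state for continuous outcomes either of the following:

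- The 6-month value is the dependent variable. Arm, the participant's baseline value of the same outcome and the RC mean of that baseline value are fixed effects always kept in the model, outside stepwise selection, with the listed confounders and the random effects for clustering.
- The two-wave mixed model is kept with a common baseline mean across arms. This is equivalent for efficiency, but it relies on the arms sharing one baseline mean.

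In both cases, keep the unconstrained arm-by-time (change) contrast as a sensitivity analysis, because only five districts were allocated.

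The cost is one sentence and one or two fixed effects, with no new data, visits or participants. In the covariate version, women without a 6-month value do not enter the main model, and missing baseline values need simple imputation. Recruitment was still open when the article was submitted, so at that point the choice could be fixed before outcomes were known.

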### Study procedure

#### Recruitment of RCs

Singapore is divided into five geographical districts, as seen in Additional file 2 [22, 23], which are all similar in terms of socioeconomic status [24]. To enhance the chance of recruiting participants into the intervention programme, three out of the five districts were randomly allocated to the intervention cluster (by drawing names from a bag) and the remaining two districts to the control cluster. The process resulted in the intervention sites (districts: 2-North West, 3-Central, and 5-South East) and control sites (districts: 1-South West, and 4-North East). Sixty RCs (intervention *n* = 30, control *n* = 30) will be randomly selected from these geographical districts. Due to the differences in the number of RCs within the districts, approximately 9–12% of the listed RCs in each district will be chosen using computer-generated random numbers. These RCs will have a minimum separation distance of 4 km to avoid risk of contamination between intervention and control groups. The recruitment process will continue until 30 control and 30 intervention RCs consent to take part in the study. The participants will all be blinded to their group status (intervention and control) during the recruitment and intervention period.

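### Stepwise entry of every variable in the confirmatory mixed model leaves the arm effect to a p-value rule and contradicts the stated adjustment for six named confounders

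*Protocol article*

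**What the plan says.** All of the relevant model text is in the protocol article, Statistical analysis.

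- Confirmatory model: "Multi-variable mixed regression analyses will be used to confirm the effects of the proposed intervention", taking account of the two time points and of "the clustering of the observations".
- Selection rule, in the next sentence: "All variables will be entered using the stepwise regression".
- Adjustment, in the sentence after that: "The regression model will also account for effects of potential confounders", listed as age, ethnicity, education, marital status, medication and housing type.
- Earlier in the same paragraph, after the sentence on descriptive statistics: "Non-parametric statistics will be applied whenever non-normality of the outcomes is detected".

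On allocation, Recruitment of RCs says that "three out of the five districts were randomly allocated to the intervention cluster", with the other two going to control.

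**The concern.** Stepwise entry keeps a term only if it passes a significance threshold. As worded, the rule covers every variable, including the arm and arm-by-time terms that carry the intervention effect. A trial has to report that effect with its interval whatever the p-value. Under this rule a non-significant effect leaves the model unreported, and a retained effect is one that has already passed a filter.

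The rule also conflicts with the promise to adjust for six named confounders, because a confounder that fails the threshold is not adjusted for. The final model's standard errors treat it as if it had been chosen in advance.

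The non-parametric rule is a lesser matter. It does not say whether it covers descriptive comparisons only or can also replace the clustered model for a non-normal outcome.

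**Working it through.** **Inputs from the protocol.** 480 women analysed, 240 per group (Sample size determination). 60 RCs, hence 480/60 = 8 women per RC at follow-up. The attrition step reproduces: 480/(1 − 0.20) = 600. The plan gives no figure for the effect of selection, so there is none to reproduce.

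**Assumptions, not in the protocol.** Continuous outcome with residual SD 1; entry at p < 0.05 and removal at p > 0.10; arm effects of 0.20 and 0.256 SD; six covariates with equal coefficients of 0.08 or 0.10 SD per SD; imbalance of 0 or 0.2 SD on all six; ICC 0.02-0.05. The simulations use ordinary regression without repeated measures or RC effects, so they show the mechanism and not the planned model itself.

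**1. Arm term, normal theory.** SE = 2/√480 = 0.0913. With μ = effect/SE, P(kept) = Φ(μ − 1.96), and the mean kept estimate divided by the true effect is 1 + φ(1.96 − μ)/[μ·P(kept)].

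- Effect 0.256: μ = 2.80, P(kept) = 0.80, ratio = 1 + 0.279/(2.80 × 0.80) = 1.12. The arm is dropped in 20% of trials.
- Effect 0.20: μ = 2.19, P(kept) = 0.59, ratio = 1 + 0.388/(2.19 × 0.59) = 1.30. The arm is dropped in 41% of trials.

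**2. Arm term, simulated stepwise selection.**

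| True effect | Covariate coefficient | Imbalance | Arm kept | Mean when kept | Excess |
|---|---|---|---|---|---|
| 0.256 | 0.10 | 0 | 77% | 0.285 | 0.285/0.256 = +11% |
| 0.256 | 0.10 | 0.2 SD | 85% | 0.314 | 0.314/0.256 = +23% |
| 0.20 | 0.08 | 0 | 58% | 0.263 | 0.263/0.20 = +32% |
| 0.20 | 0.08 | 0.2 SD | 70% | 0.283 | 0.283/0.20 = +42% |

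In the last row, the 95% interval covered the true effect in 90% of the runs that kept the arm.

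**3. Comparator.** In a rerun of the 0.20 SD set-up, the forced model's significant results with balanced covariates had the same mean as the stepwise results (0.263) and the same frequency (57.2%). With imbalance the means were 0.265 forced and 0.283 stepwise, and 0.283/0.265 is about 7% higher. The difference is that the forced model reports every estimate: over all runs of the 0.256 SD imbalanced scenario it averaged 0.258.

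**4. Confounders.** SE = 1/√480 = 0.0456. A coefficient of 0.10 gives 0.10/0.0456 = 2.19, so each covariate is kept with probability about 0.59. All six are kept with probability about 0.591⁶ = 0.043. The simulation gave 3-5%.

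**5. Type I error with no true effect.** Balanced: 5.0% stepwise against 5.3% forced, and 5.2% stepwise in the other simulation. All six covariates 0.2 SD apart: 6.7% against 6.0% (coefficient 0.10, 600 runs) and 8.2% against 5.3% (coefficient 0.08, 3,000 runs).

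**6. Secondary point: a rank test that ignores RCs.** Type I error = 2[1 − Φ(1.96/√(1 + 7·ICC))].

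- ICC 0.02: √1.14 = 1.068, giving 6.6%.
- ICC 0.05: √1.35 = 1.162, giving 9.2%.

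A Mann-Whitney simulation with 30 against 30 RCs of 8 women gave 7.1% and 9.8%.

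**The case against.** The best defence is that the stepwise sentence is loose writing. The authors may mean that further candidate variables are screened while arm and the six confounders stay in, and a full analysis plan may say so. That may be the intention, but the sentence says all variables, and a plan that forced these terms would have to overrule the published text.

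Four stronger readings are tempting, and the protocol does not support them.

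- **Stepwise selection exaggerates the effect by 32-42%.** Most of that is the ordinary significance filter at an assumed 0.20 SD effect with about 59% power. Significant results from a forced model show the same excess when covariates are balanced. At 0.256 SD the excess is 11-23%.
- **False positives are inflated.** This appears only under assumed imbalance, in the same direction on all six covariates. The protocol describes the districts as similar in socioeconomic status, which bears on education and housing. With five allocated units, imbalance is possible but not shown to be likely.
- **Clustering is lost.** The non-parametric sentence follows the one on descriptive statistics, names no test and does not say that it replaces the mixed model. It also cannot apply to the binary PA outcome used for power. What stands is an ambiguity.
- **Post-intervention medication is adjusted for.** Procedure says that "both the pre and post survey will document all those who are on medication" and links this to a subgroup analysis. Nothing says that the later value enters the model.

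**Conclusion.** The concern holds for the stepwise sentence, which is enough by itself. It contradicts the sentence after it and, taken literally, makes reporting of the primary comparison depend on its p-value. The harm falls mainly on the estimate, its interval and the promised adjustment, and much less on type I error.

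With balanced covariates the reported effect is about 11-13% too large at roughly 80% power and about 30% too large at roughly 59% power. At least one listed confounder is usually left out if the coefficients are near 0.10 SD. These sizes rest on the assumed effects, coefficients and thresholds. The contradiction itself rests on the text alone.

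The non-parametric rule needs clarification only. An unclustered rank test, if one were used for a confirmatory comparison, would have a type I error of about 7-9% at an assumed ICC of 0.02-0.05.

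**What to change.** Delete the stepwise sentence. State that every confirmatory mixed model contains arm, time, arm-by-time and the six prespecified confounders at their baseline values, whatever their p-values, and that the arm effect is always reported with its interval.

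For the non-parametric rule, state either that it applies to descriptive comparisons only, or that any confirmatory analysis of a non-normal outcome keeps the RC clustering and the repeated measures.

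Both changes are wording, and no sample size figure changes. The adjustment uses more than six degrees of freedom, because several covariates are categorical (the Background alone names three ethnic groups), but this is small against 480 women.
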